### Cluster randomized controlled trial

#### Study design and randomization

The effectiveness of the BEAR intervention will be studied in a two-armed cluster RCT (ratio 44:44). Well-baby clinic locations in the Nijmegen area in the Netherlands will be randomly assigned to either the BEAR or Care-as-usual (CAU) condition. Before randomization, the well-baby clinics will first be matched based on two characteristics (amount of children visiting that well-baby clinic and ethnicity/social-economic background of the specific area) to ensure an equal distribution in the two groups. By coin flipping, the well-baby clinics are at random assigned to either the BEAR condition or CAU. Consequently, the study is open-labeled; both participants (children and parents) and the therapist know to which condition the participant is assigned through cluster randomization. However, for the primary outcome measure, our assessors rating parent–child interaction are unaware of group allocation (see Table 2).

**Table 2 Tab2:** Outcome measures from baseline to follow-up

Measurement	Time^a^	Instrument	Informant	Blind to group status?

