#### Sample size and power

The justification of sample size is calculated based on the primary hypothesis that the BEAR intervention will improve the child’s total joint engagement (measured on a 7-point Likert scale) at the end of treatment. In a comparable study by Kasari et al. [44] with joint engagement as the primary outcome as measured in total seconds spent in joint engagement, a Cohen’s d effect size of 0.21 was found in difference in joint engagement at endpoint. We assume our effect size to be slightly lower than in the study of Kasari et al., due to a shorter duration of the BEAR intervention and the use of an ordinal variable instead of an continuous one. Based on the variance of the treatment effect, a power analysis on an alpha level of 0.05 (two sided) lead to an estimated sample size of 40 participants per group, with a power of 0.88. To allow for 10% drop out 44 participants per group (total *N* = 88) will be recruited.

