#### Statistical analysis

Data will be analyzed and reported in accordance with CONSORT guidelines. Baseline demographics (IQ, gender, age) and clinical characteristics (severity of symptoms as measured by the CoSoS) of the BEAR and CAU groups will be compared by chi-squared tests to check whether cluster randomization has led to two even groups. For the cluster RCT, all primary analyses will be intention to treat (ITT) using (generalized) linear mixed effects model for repeated measures with a random effect for cluster. Correlation of measurements (T1, T2, T3) within subject will primarily be modelled by a random effect of subject nested within clusters unless this results in insufficient fit, in which case other covariance structures will be investigated. Fixed effect in the model for baseline covariates, time and interaction with treatment condition will be included. For cost effectiveness analysis, all cost data will be accumulated. Cost differences between the two conditions will be compared. Incremental cost-effectiveness ratios will be calculated by dividing the difference in total costs by the difference in the WEMWBS.

Data collection started just before the COVID-19 pandemic. During a lockdown period where home visits were not possible because of COVID-19 restrictions, small changes were made in collecting the data and providing the BEAR intervention. Due to this, a sensitivity analysis will be undertaken, excluding participants included during the first lockdown.

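### The stated power of 0.88 makes no allowance for clustering although clinics are randomised, so it is not supported as the power of this cluster design; the size of the loss cannot be known from the article

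*Protocol article*

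**What the plan says.** Under Study design and randomization, the unit of allocation is the clinic: "Well-baby clinic locations in the Nijmegen area in the Netherlands will be randomly assigned to either the BEAR or Care-as-usual (CAU) condition". Clinics are matched on two characteristics and then allocated by coin flip. Under Participants, families from outside the region are instead randomised individually; their expected number is not given.

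Under Statistical analysis, the primary analysis is an intention-to-treat "generalized) linear mixed effects model for repeated measures with a random effect for cluster". A random effect of subject nested in cluster covers T1, T2 and T3, and the fixed effects are baseline covariates, time and an interaction with treatment condition.

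Under Sample size and power, the trial is sized on the hypothesis that "the BEAR intervention will improve the child’s total joint engagement (measured on a 7-point Likert scale) at the end of treatment". The reference study's Cohen's "d effect size of 0.21 was found in difference in joint engagement at endpoint", and the authors add: "We assume our effect size to be slightly lower than in the study of" that reference trial. The calculation is described as "Based on the variance of the treatment effect", "a power analysis on an alpha level of 0.05 (two sided"), and yields 40 per group with power 0.88. The only later step is for dropout: "To allow for 10% drop out 44 participants per group (total" N = 88).

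**The concern.** Children from the same clinic tend to resemble one another, because they share a neighbourhood, the same staff and the same local care. When the clinic is allocated, that resemblance can enlarge the variance of the treatment comparison, and the comparison may rest on the number of clinics more than on the number of children. A power figure for such a trial needs at least the number of clinics, their size and an ICC. The sample-size section has none of these, and the number of clinics appears nowhere in the article.

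What is at stake is how the result will be read. If the trial shows no clear effect, readers will weigh that against a stated power of 0.88, which the design may not have.

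**Working it through.** **Inputs from the article:** 40 evaluable per group, two-sided alpha 0.05, power 0.88, d slightly below 0.21, dropout 10%, 44 recruited per group.

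**Inputs assumed because the article gives none:** 8 to 40 clinics in total, equal cluster sizes, 80 evaluable children, ICC 0.01 to 0.10.

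**1. The article's own figure.** With n = 40 per group the noncentrality is d × √(n/2) = d × √20 = 4.472d.
- At d = 0.21: 0.21 × 4.472 = 0.939, and power ≈ Φ(0.939 − 1.960) = 0.15. Power 0.88 at this d needs 446 per group.
- For 0.88 at n = 40: d = (1.960 + 1.175)/4.472 = 0.70 by the normal approximation, 0.71 by the noncentral t with 78 degrees of freedom.

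So 40 per group at 0.88 does not follow from the cited d as a plain two-group comparison. The figure can be approached by reading the effect as Cohen's f in a two-time-point group-by-time F test (f = 0.21 with correlation 0.3 gives 0.88). That is not the stated measure, and it too is an individual-level calculation.

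**2. Is a design effect hidden in the step to 44?** 40 × 1.10 = 44, so dropout accounts for the whole step. (Dividing instead, 40/0.9 = 44.4, gives 45, a trivial difference.) Nothing is left over for clustering.

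**3. What clustering would do to an endpoint comparison.** Take an effect that does give 0.88 without clustering, d = 0.71. With K clinics in total, m = 80/K, design effect DE = 1 + (m − 1) × ICC, effective n per arm = 40/DE, and power from the noncentral t with noncentrality 0.71 × √(20/DE).

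| Clinics (total) | m | ICC | DE | Effective n per arm | Power, 78 df | Power, K − 2 df |
|---|---|---|---|---|---|---|
| 8 | 10 | 0.01 | 1.09 | 36.7 | 0.852 | 0.718 |
| 8 | 10 | 0.05 | 1.45 | 27.6 | 0.740 | 0.598 |
| 8 | 10 | 0.10 | 1.90 | 21.1 | 0.624 | 0.490 |
| 12 | 6.7 | 0.01 | 1.06 | 37.9 | 0.862 | 0.795 |
| 12 | 6.7 | 0.05 | 1.28 | 31.2 | 0.791 | 0.715 |
| 12 | 6.7 | 0.10 | 1.57 | 25.5 | 0.707 | 0.629 |
| 20 | 4 | 0.01 | 1.03 | 38.8 | 0.871 | 0.841 |
| 20 | 4 | 0.05 | 1.15 | 34.8 | 0.833 | 0.800 |
| 20 | 4 | 0.10 | 1.30 | 30.8 | 0.785 | 0.750 |
| 40 | 2 | 0.01 | 1.01 | 39.6 | 0.877 | 0.868 |
| 40 | 2 | 0.05 | 1.05 | 38.1 | 0.864 | 0.855 |
| 40 | 2 | 0.10 | 1.10 | 36.4 | 0.848 | 0.839 |

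At d = 0.21 the same assumptions give 0.09 to 0.15.

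**4. What it would do to a treatment-by-time contrast.** Write the outcome of child i in clinic j at time t as fixed effects + u_j + v_ij + e_ijt. The change from T1 to T2 is then fixed effects + e_ij2 − e_ij1: the clinic and child intercepts both cancel. If the model includes a treatment main effect, generalised least squares for 80 children in 8 to 20 clinics, ICC 0.02 to 0.10 and within-child correlation 0.3 to 0.7 (all assumed) gives a variance inflation of exactly 1.00 for the T2 interaction. If baseline means are constrained equal, it is about 1.01 to 1.26. If clinics also differ in their change, a term w_j stays in the contrast and the inflation becomes 1 + (m − 1) × (ICC of change), so a loss like that in step 3 returns.

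**The case against.** The strongest reply is that the endpoint formula does not fit the model in the Statistical analysis section. That model uses all three time points, and if the tested effect is the treatment-by-time interaction, random intercepts drop out (step 4). This stands, and it limits the size of the point: the design effects up to 1.90 and the clinics-minus-2 degrees of freedom apply to a comparison of endpoint means, or when clinics differ in change. It does not rescue 0.88. The sample-size section frames the hypothesis at end of treatment, makes no appeal to cancelling intercepts, and assumes nothing about differences between clinics in change.

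Matching of clinics, use of the T1 measurement and the individually randomised families could all reduce the loss. That is also fair, but the calculation takes credit for none of them.

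Three stronger readings are tempting and not supported.
- A reader might infer that the clinics are few. The article gives no number; with 40 clinics power stays at about 0.84 to 0.87 on clinic degrees of freedom.
- A reader might infer that the planned test has an inflated type I error because clustering is ignored. The analysis does include a cluster effect, and the choice of degrees of freedom is ordinary detail for an analysis plan that is not shown.
- A reader might infer that the calculation was demonstrably made for individually randomised children. Since 40 per group cannot be reproduced from the stated d, and the variance used is not defined, that is likely but not proven. What can be said is that nothing stated allows for clustering.

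**Conclusion.** The point holds as one of support for a stated figure: 0.88 is not established as the power of a trial that randomises clinics. This comes on top of the separate effect-size mismatch, which is the larger problem.

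The direction is firm for an endpoint comparison: any ICC above zero with more than one child per clinic puts power below what individual randomisation would give. The size is not known. It ranges from almost nothing (many clinics, small ICC, or an interaction contrast with clinics alike in change) to a fall from 0.88 to about 0.5 (8 clinics, ICC 0.10, endpoint means, 6 degrees of freedom). All of these figures assume equal cluster sizes and 80 evaluable children. This should be fixed, but it does not by itself invalidate the design.

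**What to change.** Keep N = 88 and restate the power statement. Give the actual number of clinics and the expected children per clinic, a stated ICC range such as 0.01 to 0.10, and the contrast that the primary model will test. Account for the individually randomised families, and report the resulting power and detectable difference. For an endpoint comparison, the effect detectable at 0.88 grows by √DE: from 0.71 to 0.71 × √1.90 = 0.98 at the worst assumed case, before any degrees-of-freedom correction.

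In the model, add a cluster-by-time random term, or otherwise let clinics differ in change. If the clinics turn out to be few, use small-sample degrees of freedom for the treatment test (Kenward-Roger or Satterthwaite for a linear model, or a suitable equivalent if a generalized model is fitted).

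The cost is revised text, one model term and a software option. The stated power will be less favourable and intervals slightly wider. No extra participants are needed.

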#### Data collection and management

Data collection follows the European General Data Protection Regulation. After inclusion, participants will receive an unique code number in order to anonymize all data. Non-anonymous data, for example informed consent forms, are locked in a closed cabinet and saved in protected folders, only accessible by appointed members of the research team. In order to collect and store data from the questionnaires, Castor Electronic Data Capture (Castor EDC, 2021) and QuestManager (version 5.6) software are used. Video-data will be anonymously saved on an external hard disk, which is password protected and saved in a locker.

Parents of participants are asked to complete a number of online questionnaires (see Table 2) through the QuestManager software. Parents are only able to continue to a next questionnaire if all items are answered. To prevent missing data, a researcher will call parents as a reminder and offer support if parents encountered any problems, if they fail to complete the measurements on time. Parents may withdraw from the study at any time for any reason. If this happens, researchers will try to make a final appointment with parents in order to collect the primary outcome.

#### Statistical analysis

Data will be analyzed and reported in accordance with CONSORT guidelines. Baseline demographics (IQ, gender, age) and clinical characteristics (severity of symptoms as measured by the CoSoS) of the BEAR and CAU groups will be compared by chi-squared tests to check whether cluster randomization has led to two even groups. For the cluster RCT, all primary analyses will be intention to treat (ITT) using (generalized) linear mixed effects model for repeated measures with a random effect for cluster. Correlation of measurements (T1, T2, T3) within subject will primarily be modelled by a random effect of subject nested within clusters unless this results in insufficient fit, in which case other covariance structures will be investigated. Fixed effect in the model for baseline covariates, time and interaction with treatment condition will be included. For cost effectiveness analysis, all cost data will be accumulated. Cost differences between the two conditions will be compared. Incremental cost-effectiveness ratios will be calculated by dividing the difference in total costs by the difference in the WEMWBS.

Data collection started just before the COVID-19 pandemic. During a lockdown period where home visits were not possible because of COVID-19 restrictions, small changes were made in collecting the data and providing the BEAR intervention. Due to this, a sensitivity analysis will be undertaken, excluding participants included during the first lockdown.

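### The primary model takes T1 joint engagement as a response without stating how it is adjusted for or which contrast is primary; fitted in the usual way, it gives up precision at T2

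*Protocol article*

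**What the plan says.** The Statistical analysis section of the protocol article plans an intention-to-treat mixed model for repeated measures with a random effect for cluster. All three visits are responses: "Correlation of measurements (T1, T2, T3) within subject will primarily be modelled by a random effect of subject nested within clusters". Other covariance structures follow if the fit is poor. On the fixed part it says "Fixed effect in the model for baseline covariates, time and interaction with treatment condition will be included".

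The section does not list the baseline covariates, does not name a treatment main effect and does not say which contrast is the primary treatment effect. T1 joint engagement is not named as a covariate. The baseline variables that the section does name (IQ, gender, age, CoSoS severity) are there for comparing the two groups.

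The primary time point comes from the Sample size and power section, which concerns "total joint engagement (measured on a 7-point Likert scale) at the end of treatment", that is, T2.

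**The concern.** The primary question is about T2, and a T1 recording is scheduled for every family. How T1 enters the model decides how precise the T2 comparison is. The stated terms allow at least three versions:

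- a treatment main effect is included, and the T2 interaction is tested;
- a treatment main effect is included, and the arm difference at T2 is tested;
- no treatment main effect is included, so both arms share one T1 mean.

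The first two estimate different contrasts, and both are less precise than an analysis that adjusts for T1. The third matches baseline adjustment when there is no clustering, but nothing in the text says that the T1 means are meant to be constrained.

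The unlisted baseline covariates do not settle the matter. If T1 joint engagement is one of them while T1 remains a response, the T1 score helps to predict itself. With 40 analysable families planned per arm, precision that costs no extra data is worth securing.

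**Working it through.** **The plan's own figure.** The inputs in Sample size and power are a two-sided alpha of 0.05, "lead to an estimated sample size of 40 participants per group", "with a power of 0.88", and a reference study in which an "effect size of 0.21 was found in difference in joint engagement at endpoint". With d = 0.21 and 40 per group, power by the normal approximation is 0.154. Power of 0.88 would need 446 per group at that d, or d of about 0.70 at 40 per group. The stated power therefore does not reproduce. That is a separate and larger matter; here it only sets the scale for the power gain.

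**Assumptions.** The article gives no within-child correlation and no ICC. I take r = 0.3, 0.5 and 0.7; ICC = 0 first, then 0.05 with 10 clusters of 8; complete data; equal variances; and a random-intercept covariance over T1 to T3.

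**Variance of the T2 effect, in units of 2σ²/n, at ICC 0:**

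| Version | Formula | r = 0.3 | r = 0.5 | r = 0.7 |
|---|---|---|---|---|
| Main effect included, T2 interaction (difference in change) | 2(1-r) | 1.40 | 1.00 | 0.60 |
| Main effect included, arm difference at T2 | 1 | 1.00 | 1.00 | 1.00 |
| No main effect (common T1 mean) | 1-r² | 0.91 | 0.75 | 0.51 |
| T1 as covariate | 1-r² | 0.91 | 0.75 | 0.51 |

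The first three rows were confirmed from the generalised least squares information matrix for the T1 to T3 model.

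**Adjusted against change-based.** The ratio is (1-r²)/[2(1-r)] = (1+r)/2 = 0.65, 0.75, 0.85. The adjusted variance is thus 35%, 25% and 15% smaller. In sample-size terms, 2/(1+r) - 1 = 54%, 33% and 18% more families would be needed to make up the difference.

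**Adjusted against the arm difference at T2.** The saving is r² = 9%, 25% and 49%.

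**With clustering (ICC 0.05).** The T2 interaction stays at 1.40, 1.00 and 0.60, because a cluster effect that is constant over time cancels in the change. The arm difference at T2 rises to 1 + 7 × 0.05 = 1.35. The common-T1-mean model gives 1.037, 0.815 and 0.533. The gap to the change-based contrast is then 1 - 1.037/1.40 = 26%, 1 - 0.815/1.00 = 19% and 1 - 0.533/0.60 = 11%.

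**Power at d = 0.21, 40 per group, ICC 0.** SE = √[(2/40) × factor].

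| Contrast | r = 0.3 | r = 0.5 | r = 0.7 |
|---|---|---|---|
| Difference in change | 0.122 | 0.154 | 0.227 |
| Arm difference at T2 | 0.154 | 0.154 | 0.154 |
| Adjusted for T1 | 0.165 | 0.191 | 0.259 |

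The gain over the change-based contrast is 4.3, 3.7 and 3.2 points. Over the arm difference at T2 it is 1.1, 3.7 and 10.5 points.

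**The case against.** The strongest reply is that the article does not commit to an inefficient model. It never speaks of a difference in change, and its listed terms, taken literally, contain no treatment main effect. That is the common-T1-mean model, which at ICC 0 is as precise as baseline adjustment. A journal article may also leave the covariate list and the contrast to the full protocol or analysis plan. Both points limit the concern to how the stated model would be read and fitted. They do not remove it: a treatment-by-time model is commonly fitted with its main effects, and the text does not say that the T1 means are constrained.

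A mixed model with T1 among the responses is also standard and valid, and it keeps families with partial data. That stands in full.

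A third point is that baseline adjustment assumes equal expected T1 scores in the two arms. The Pre-study phase section says that recruiting professionals were told their clinic's condition, and the notes to Table 2 have the BEAR professional carrying out the T1 and T2 JERI assessments. Imbalance at T1 is therefore possible. This calls for a report of T1 balance, but it does not make a change-based or unadjusted contrast the better primary analysis.

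Three stronger readings are tempting and are not supported:

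- A reader might infer that the plan fixes the effect as a difference in change. It leaves the contrast open.
- A reader might take 15% to 35% as the share of the available variance reduction that is lost. It is how far the adjusted variance lies below the change-based one. The share lost would be (1-r)²/r², which is 18% at r = 0.7, 100% at r = 0.5 and 544% at r = 0.3, where change is worse than ignoring T1.
- A reader might expect large power gains. At d = 0.5 they would be 6 to 18 points (82% to 88% at r = 0.7, 47% to 65% at r = 0.3), but the article cites 0.21 and adds "We assume our effect size to be slightly lower".

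**Conclusion.** The point holds as one of precision and clarity, not bias. The plan makes T1 a response and states neither how T1 is adjusted for nor which contrast is primary. Under the usual fit with a treatment main effect, both candidate T2 contrasts are less precise than a T1-adjusted one for any r between 0 and 1 without clustering. Against the change-based contrast the shortfall is 35%, 25% and 15% of variance at r = 0.3, 0.5 and 0.7, or about 26%, 19% and 11% at ICC 0.05 with 10 clusters of 8. These figures rest on assumed values of r, ICC and cluster size, and on complete data. At the cited effect size the gain over the change-based contrast is about 3 to 4 power points, so this change does not repair the power calculation. It is still worth making, because the data are already being collected.

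**What to change.** State before analysis that the primary contrast is BEAR minus CAU in total joint engagement at T2, estimated in one of two ways:

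- **(a)** Responses: T2 and T3. Fixed effects: T1 joint engagement, T1 by time, treatment, time, and treatment by time. Random effects: clinic, and subject within clinic (or an unstructured residual covariance in place of the subject effect). The link between a child's T2 and T3 scores must be kept.
- **(b)** The planned T1 to T3 model, with the T1 means explicitly constrained to be equal across arms.

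In either case, do not enter T1 joint engagement as a covariate while it is also a response. Report T1 balance by arm, because recruiters knew the clinic's allocation.

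The cost is wording only; no extra data are needed. Option (a) needs a simple rule for families without a usable T1 video. Option (b) does not.

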7	The last session is a summary and evaluation of the learning process of child and parents. If serious concerns continue to exist, clinical assessment, diagnostic referral and/or further treatment can be advised. Specialized knowledge from the BEAR supervisor will enable to come up with an appropriate advise	Child, parent, BEAR professional	90 min

^a^The ASD expert supervises remotely throughout the entire process

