**Secondary outcome**				
Change in ASD symptoms	T1, T2, T3	BOSCC (parent)	RA ^b^	Yes
	T1, T3	BOSCC (clinician)	RA^c^	Yes
	T1, T3	ADOS-2	Clinician	Yes
Expressive language	T1, T2, T3	JERI	RA ^b^	Yes
	T1, T3	N-CDI	Parent(s)	
Adaptive functioning	T1, T3	Vineland Screener	Parent(s)	
Parental well-being	T1, T2, T3	WEMWBS	Parent(s)	
	T1, T2, T3	PSQ	Parent(s)	
Parental skills	T1,T2, T3	JERI	RA ^b^	Yes
`Satisfaction	T2	BESTE-O	Parent(s)	
	T2	BESTE-H	BEAR professional	
	T3	Satisfaction survey	Parent(s)	
Cost measurements	T1, T2, T3	Tic-P	Parent(s)	

*Bayley-III* Bayley Scales of Infant and Toddler Development, *BITSEA* Brief Infant–Toddler Social & Emotional Assessment-Revised, *SOV* Dutch version of the Autism Quotient (AQ), *JERI* Joint Engagement Rating Inventory, *BOSCC* Brief Observation of Social Communication Change, *ADOS-2* Autism Diagnostic Observation Schedule, *N-CDI* Dutch version of the MacArthur Communicative Development Inventory, *Vineland Screener* adapted version of the Vineland Adaptive Behaviour Scales, *WEMWBS* Warwick-Edinburgh Mental Well-being Scale, *PSQ* Parenting Stress Questionnaire (PSQ, in Dutch Opvoedingsbelastingsvragenlijst)*, BESTE* the Rating Scale Satisfaction and Effect questionnaire, *Tic-P* Trimbos and iMTA questionnaire on Costs associated with Psychiatric illness

^a^T1 is baseline; T2 is endpoint, eight weeks after baseline; T3 is follow-up, 24 weeks after endpoint

^b^Both the JERI and the BOSCC(parent) are assessed by the BEAR professional as part of the intervention (only at T1 and T2). At T3, both measurements are assessed by a researcher of the SCOPE project. All data will be coded by research assistants who are unaware of treatment allocation

^c^The BOSCC(clinician) is assessed by a professional examiner. Data will be coded by research assistants who are unaware of treatment allocation

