**Assessment of healthcare sources**

Direct and indirect costs as a consequence of the child’s psychiatric condition, i.e. the medical costs and productivity losses in parents are measured using the ‘Trimbos and iMTA questionnaire on Costs associated with Psychiatric illness’ (Tic-P questionnaire; [43]). Validity and reliability have been established [43]. For every participant, the duration and type of each contact as well as the type of health care worker with whom the contact was in the last 3 months will be registered as to monitor use of healthcare sources in both groups as well as to calculate the cost-effectiveness of arms. Productivity losses of parents associated with their child’s health problem or its treatment will be registered as well.

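### Tic-P at three visits with a 3-month recall leaves weeks 8 to 19 unrecorded and reaches back before baseline, so the accumulated total is not the cost of the follow-up period

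*Protocol article*

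**What the plan says.** Four statements in the protocol article fix how costs are collected and summed.

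- **Recall.** Under Assessment of healthcare sources, the duration and type of each contact and "the type of health care worker with whom the contact was in the last 3 months will be registered", partly in order to calculate cost-effectiveness. Parents' productivity losses are registered too, but no recall period is given for them.
- **Schedule.** Table 2 lists the cost measurement (Tic-P, parent-reported) at T1, T2 and T3. Footnote a of that table gives the timing: "T1 is baseline; T2 is endpoint, eight weeks after baseline; T3 is follow-up, 24 weeks after endpoint".
- **Summation.** Statistical analysis: "For cost effectiveness analysis, all cost data will be accumulated".
- **Ratio.** The same section obtains the incremental ratio by "dividing the difference in total costs by the difference in the WEMWBS".

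Visit timing is not the same throughout. The Study phase steps under Procedures put T2 at about eight to ten weeks after baseline and T3 six months after endpoint. The Methods part of the Abstract gives T3 as after six months, which can be read as counted from the start of the study.

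**The concern.** Cost-effectiveness is one of the stated aims of the trial, and the Abstract promises a societal perspective. A total cost for that purpose should cover the period over which the arms are compared, once and without holes. Three 3-month windows placed at weeks 0, 8 and 32 cannot do that. The first lies wholly before baseline, the second starts before baseline and overlaps the first, and the third begins well after the second ends.

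The hole opens directly after the BEAR programme finishes. Table 1 says that clinical assessment, referral or further treatment can be advised at the last home visit. The Care-as-usual section describes a pathway that varies from no treatment to specialised care. Equal costs in the two arms during the unrecorded weeks therefore cannot be assumed. If they differ, the numerator of the ratio is biased.

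**Working it through.** The article gives no coverage figure to reproduce, so the check is on the recall windows.

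**Inputs.** T1 = week 0, T2 = week 8, T3 = 8 + 24 = week 32 (Table 2, footnote a). Recall r = 3 months, taken as 13 weeks, with 12 weeks as a sensitivity value. A visit at week t covers weeks t - r to t.

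**Windows with r = 13.**
- T1: -13 to 0
- T2: 8 - 13 = -5, so -5 to 8
- T3: 32 - 13 = 19, so 19 to 32

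**Coverage.**
- Weeks recalled in total: 3 × 13 = 39.
- Before baseline: 13 (T1) + 5 (T2) = 18, or 18/39 = 46%. Weeks -5 to 0 appear twice.
- Follow-up weeks recorded: 8 + 13 = 21 of 32 (66%).
- Follow-up weeks not recorded: (T3 - r) - T2 = 19 - 8 = 11 of 32 (34%).

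**Other readings of the timing.** Gap = T3 - r - T2, with six months taken as 26 weeks. A reading of 24 weeks from baseline is included as the shortest case.

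| Reading | T2 | T3 | Gap, r = 13 | Gap, r = 12 |
|---|---|---|---|---|
| Table 2 | 8 | 32 | 11 of 32 | 12 of 32 |
| T2 at week 10, T3 24 weeks later | 10 | 34 | 11 of 34 | 12 of 34 |
| Procedures, early T2 | 8 | 34 | 13 of 34 | 14 of 34 |
| Procedures, late T2 | 10 | 36 | 13 of 36 | 14 of 36 |
| T3 at 26 weeks from baseline | 8 | 26 | 5 of 26 | 6 of 26 |
| T3 at 26 weeks from baseline | 10 | 26 | 3 of 26 | 4 of 26 |
| T3 at 24 weeks from baseline | 8 | 24 | 3 of 24 | 4 of 24 |
| T3 at 24 weeks from baseline | 10 | 24 | 1 of 24 | 2 of 24 |

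A gap remains in every row. With T2 at week 10 and r = 13, the pre-baseline weeks fall only from 18 to 13 + 3 = 16 of 39.

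**What each defect does to the cost difference.** Let the weekly cost difference (BEAR minus care as usual) be a in weeks 0 to 8, b in weeks 8 to 19, c in weeks 19 to 32, and i before baseline. Then

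- true follow-up difference = 8a + 11b + 13c
- accumulated difference = 18i + 8a + 13c
- error = 18i - 11b

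With comparable arms, i is zero in expectation, so the first term is noise plus any baseline imbalance. The second term is a bias whenever b is not zero. Three examples with assumed weekly values, for illustration only:

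| a | b | c | i | True | Accumulated |
|---|---|---|---|---|---|
| 100 | 100 | 100 | 0 | 3200 | 2100 |
| 100 | -40 | -40 | 0 | -160 | 280 |
| 0 | 0 | 0 | 20 | 0 | 360 |

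The first understates the extra cost of BEAR. The second turns a saving into an extra cost. The third produces a difference from baseline imbalance alone.

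**The case against.** The strongest reply is that one condensed sentence is being read too literally. Accumulating all cost data may mean adding the cost categories (medical costs and productivity losses). A fuller economic plan, not shown, may drop T1, trim the overlap and interpolate. That is fair for the pre-baseline weeks, where analysis can repair the sum. It does not dispose of the gap: the article fixes both schedule and recall, and no later plan can recover contacts that were not asked about. It could only extrapolate.

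Second, the 46% is not a measure of error. Pre-baseline costs cancel in expectation between comparable arms. This stands.

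Third, the 3-month recall is stated for health care contacts only, so the gap is not shown for productivity losses. This also stands.

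A reader might go further and infer that the omission favours BEAR, because referrals advised at the last visit fall in the gap. The article does not support a direction. Care as usual also includes referral, assessment and specialised daycare, whose costs fall in the same weeks. The Background reports long waiting lists, so care advised at the last visit may begin only within the T3 window.

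A reader might also object that remote expert supervision is left uncosted, or that WEMWBS is the wrong denominator. The article does not say that intervention delivery is costed from parent report alone, and parental well-being is a stated secondary objective. The first would be missing detail and the second a preference.

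**Conclusion.** The point holds for the collection and summation of health care costs. Under every reading of the visit timing, the accumulated Tic-P data differ from the cost of the follow-up period. On the Table 2 timing with a 13-week recall, 11 of 32 follow-up weeks are unrecorded, and the T1 window plus about 5 weeks of the T2 window precede baseline. The gap is 13 of 34 to 36 weeks on the Procedures timing, and about 1 to 6 weeks if T3 is six months from baseline.

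The two defects differ in weight. The pre-baseline weeks add noise and any baseline imbalance. The unrecorded weeks bias the difference if the arms differ in cost during them, by an amount and in a direction that cannot be derived from the article. The result assumes that the recall is applied as stated at each visit and extends to productivity losses only if the same recall is used there. This is a secondary economic analysis, and joint engagement as primary outcome is untouched.

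**What to change.** 1. Define total cost as the cost from baseline to T3.
2. Keep T1 costs out of the sum and use them only as a baseline covariate.
3. Count BEAR sessions once, from delivery records, and take any that parents reported out of the T2 Tic-P. Only then apportion the remaining T2 contacts to the weeks since baseline (8/13 for T2 at week 8). The order matters: all BEAR sessions fall after baseline, so scaling the whole T2 report by 8/13 would remove 5/13 = 38% of them.
4. Estimate the unrecorded weeks between T2 and T3 from the adjacent T2 and T3 weekly cost rates, vary the assumed rate in a sensitivity analysis, and state in the report that these weeks are extrapolated.
5. Reconcile the T3 timing in the Abstract, Table 2 footnote a and the Procedures section, and state the recall period for productivity losses.
6. Optionally, for participants who have not reached T3, add a question on the time since the previous assessment and keep the 3-month item, so that the instrument stays comparable across participants.

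The cost is analysis work, access to delivery records and an explicit extrapolation assumption. If the question is added, some participants face a longer recall. Follow-up was expected to end in 2023, so step 6 helps only those still to be seen; steps 1 to 5 do not depend on new data from parents.
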